#### Demographic measures

For both AYA and support-person participants, information on age, sex, education, employment status, family structure, and the AYAs’ diagnosis and treatment regimen will be collected using standardised items adapted from the Childhood Cancer Survivor Study questionnaire items 
[66].

#### Psychosocial functioning

There is little consensus regarding the relative superiority of generic versus disease-specific psychosocial measures in psycho-oncology. Disease-specific measures often appeal to researchers due to the difficulty ascertaining ‘clinical’ change in populations that may only be distressed at sub-clinical levels 
[67,68]. However, generic psychological measures facilitate comparison to healthy norms, which is clinically and empirically advantageous 
[29]. As recent reviews have not shown disease-specific measures to provide a systematic advantage in detecting intervention effects 
[29], the Recapture Life-AYA trial uses both generic and disease-specific indicators of psychosocial functioning.

Quality of life (QoL) was selected to be the primary psychosocial outcome variable, as this enabled the measurement of specific functional issues specific to early cancer survivorship. The Impact of Cancer Scale (IOCS) 
[69,70] was chosen to measure QoL, and measures aspects of cancer survivorship such as: Life Challenges, Body/Health, Talking With Parents, Personal Growth, Thinking/Memory Problems, Health Literacy, Socializing and Financial Problems. Although this measure has been validated in 18–39 year old AYA cancer survivors, its readability and content relevance for the younger AYAs in the Recapture Life-AYA trial was confirmed through assessments pilot testing with consumer representatives aged 15–18 years. The Flesch-Kincaid reading level was also assessed as being at Grade 6.15.

There will be a number of secondary psychosocial functioning measures. The *Psychosocial Adjustment to Illness Scale–Interview Form (PAIS)*[71] will be administered to participants over the telephone at each time point. The PAIS assesses psychosocial adjustment of patients to cancer across seven domains including: Health Care Orientation, Vocational Environment, Domestic Environment, Sexual Relationships, Extended Family Relationships, Social Environment and Psychological Distress.

The *Depression, Anxiety and Stress Scale-Short Form (DASS–21)*[48] is included as a brief, generic measure of other relevant symptoms of psychological distress. This scale shows strong internal consistency and reliability for each subscale 
[48,72,73]. The DASS-21 has been validated in Australian adolescents 
[72], and in cancer patients 
[74].

AYA participants will also complete the *KIDCOPE (Older version)*[75], in order to assess their positive and negative coping approaches.

#### Family functioning measures

Both AYA participants and support-person participants will complete the general functioning, family communication, and problem-solving subscales of the *McMaster Family Assessment Device*[76].

#### Intervention engagement and impact

To assess AYAs’ mood in a more dynamic manner across the intervention, AYAs will complete the emotion thermometers tool 
[77] each week, 24-hours prior to participating in the weekly intervention session (RL or PSG). At the same time, AYA participants will complete the 6-point *Homework Compliance Scale*[78], to assess compliance with the home practice exercises. Support persons will also complete the weekly emotion thermometers tool, included with their weekly psycho-educational email.

#### Satisfaction with intervention

The brief *Youth Satisfaction Questionnaire* (YSQ) 
[79,80], will be completed by both AYA and support-person participants to assess their satisfaction with care and overall experience. At T2 and T3 assessments, this will be followed by 10 ratings of specific intervention elements to determine their acceptability (RL and PSG). Open-ended questions will also be used to elicit their experiences in the program and suggestions for improvement.

#### Feasibility outcome measures

The feasibility of Recapture Life-AYA will be determined through a number of indices, including: (i) the proportion of participants who would have been able to participate in Recapture Life-AYA without the provision of any additional technology; (ii) the time taken to complete and return questionnaires at each time point; (iii) the study response rate; (iv) the attrition rates of the study as a whole and to the Recapture Life-AYA arm specifically; (v) completion rates for the two intervention arms; (vi) the proportion of AYAs who nominate a support person to participate. The feasibility of implementing the Recapture Life-AYA study procedures will be assessed by examining the flow through the study (from opt-in to T3 assessment completion), using medians and ranges at each point.

### Data management and analysis

All measures (except the telephone interview) will be administered online, through Lime Survey^TM^ at all timepoints. This secure tool enables participants’ data to be downloaded to files amenable to statistical analysis, such as the Statistical Package for the Social Sciences (SPSS, by IBM).

#### Statistical analyses

This trial will employ ‘Intention to treat’ and ‘as treated’ analyses. Analyses will be based on mixed random-intercept models which will assess differences between the groups in terms of change in QoL from T1 to T2, and from T1 to T3. Random intercept models, which utilise maximum-likelihood estimation, provide more efficient estimates of effects with unbalanced data than the traditional repeated measures approach 
[81]. Analyses will follow recent commentaries on the best way to manage missing data by employing multiple imputation techniques 
[82]. Multiple regression analyses will also be conducted using T1 data to identify demographic and other factors that contribute to treatment outcome. Multiple comparisons will be used to test a priori and post-hoc hypotheses, appropriately adjusted to maintain the nominated Type I error rate.

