### Participants

This study will recruit 90 AYA participants from hospitals across Australia in the first 1–6 months after treatment completion. AYAs will also have the option of inviting a support person to receive information and updates through the Recapture Life-AYA study, however as this is optional no ‘target’ sample size of support persons has been set. The AYA sample size will allow differences of a medium to large effect size (*d* = 0.65, the difference in change from T1 to T2 for any pair of groups, standardised on the pooled within-group standard deviation) on the primary outcome variable (QoL) to be detected with a power of 80% at a significance level of 0.05 (two-tailed). This effect size is clinically significant 
[42] and is based on other RCTs of similar interventions for AYAs with chronic illness 
[43-45]. It is anticipated that approximately 220 patients will need to be approached to achieve a final sample of 90 participants (assuming a response rate of 50% and attrition rate of 20%, based on previous interventions with AYA) 
[19,46,47].

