### Interventions

#### Recapture Life-AYA intervention

Recapture Life is guided by the *Adolescent Resilience Model* (ARM) 
[56]. Based on extensive research in AYAs with cancer, the ARM conceptualises resilience in young people as a multifaceted process, involving the interaction of individual, family and social-level risk and protective factors to determine AYAs level of resilience, and ultimately their quality of life. Additional file 
1: Table S1 identifies the key components of this model and the way in which these processes are targeted in Recapture Life. Several adaptive processes are implicated by this model including AYAs’ ability to: enact positive coping behaviours, negotiate uncertainty in illness and cancer-related distress, reappraise the experience in order to derive adaptive meaning from it, and seek and maintain support from family and friends. To our knowledge, only one other published intervention has utilised this framework in AYAs 
[57,58], however this music therapy intervention is delivered individually to AYAs receiving stem-cell transplants whilst on treatment. As such, this program may not offer the skill-building and peer support that we hypothesise are crucial to promote adaptation into survivorship. In addressing these component processes of resilience after cancer, our manualised program derives its core mechanisms of change from CBT techniques.

The primary goals of the Recapture Life-AYA intervention are to improve QoL, reduce distress and facilitate healthy coping in young cancer survivors. Participants randomised to Recapture Life-AYA will participate in six, weekly, 90-minute sessions facilitated by a psychologist. Each group will comprise the psychologist plus a minimum of 3 and a maximum of 5 AYAs with mixed diagnoses and genders, separated into two age groups: 15–17 and 18–25 years. Each Recapture Life-AYA module applies CBT techniques to the key domains of concern identified by our team’s previous work 
[59,60] (See Additional file 
2: Table S2).

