#### Peer-support group (active control)

The PSG control is delivered in an identical manner to Recapture Life-AYA (via WebEx, 3–5 participants/group, with the same facilitator, divided into 2 age groups), frequency of contact (six weekly 90-minute sessions), and the availability of peer-based group discussion. Like Recapture Life-AYA, it also involves age-appropriate supportive counseling to normalise the range of AYA experiences 
[61] and provides AYAs an opportunity to give and receive emotional/practical support. During each session, AYAs are encouraged to exchange information about a nominated topic (closely match those addressed in Recapture Life-AYA, e.g. ‘relationships’). The key distinction between Recapture Life-AYA and the PSG control is that the PSG does not include directive, structured teaching of specific, CBT-based coping skills. The PSG also does not include the support-person element where they receive psychoeducation and weekly emails alongside the AYA online sessions. The PSG in this trial will adhere to best practice guidelines 
[62] and is manualised to ensure standardization across all sessions.

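### The two active arms are delivered in therapy groups of 3 to 5, but neither the named analysis model nor the power figure has a therapy-group level, so standard errors are too small if outcomes within a group are positively correlated

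*Protocol article*

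**What the plan says.** **Delivery.** Randomisation is individual (Randomization). RL then runs as six weekly 90-minute sessions, and "Each group will comprise the psychologist plus a minimum of 3 and a maximum of 5 AYAs" (Recapture Life-AYA intervention). The PSG arm has the same format: "via WebEx, 3–5 participants/group, with the same facilitator, divided into 2 age groups" (Peer-support group). Waitlist participants have no group until Week 7, when they are randomised to RL or PSG (Procedures). The design is therefore partially nested at T2: two arms are grouped and one is not.

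**Analysis.** "Analyses will be based on mixed random-intercept models which will assess differences between the groups" in change in quality of life from T1 to T2 and from T1 to T3 (Statistical analyses). The stated reason is efficiency with unbalanced data compared with repeated-measures analysis. Missing data are to be multiply imputed. No therapy-group term is mentioned.

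**Power.** "This study will recruit 90 AYA participants from hospitals across Australia". "The AYA sample size will allow differences of a medium to large effect size", namely d = 0.65, with 80% power at a two-sided 0.05 level. The effect is defined as "the difference in change from T1 to T2 for any pair of groups, standardised on the pooled within-group standard deviation". No ICC, group size or design effect is given.

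**The concern.** People who share six sessions of peer discussion may come to resemble one another in outcome. The article's own rationale makes this plausible. Its Background wants to know how far peer discussion drives adaptation. Its Discussion expects PSG conversations to turn spontaneously to coping skills, and whatever arises in a session is shared by everyone in it. A single facilitator removes differences between therapists, but not differences between groups.

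A participant-level intercept accounts for repeated measurements on one person. It does not account for correlation between people in the same therapy group. If that correlation is positive and ignored, tests reject too often. RL versus PSG, the second hypothesis, is affected most because both of its arms are grouped. The promised multiplicity adjustment cannot hold the type I error rate if the standard errors feeding it are too small. Power is overstated for the same reason.

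**Working it through.** **Inputs from the article:** 90 participants in three arms; d = 0.65; two-sided 0.05; groups of 3 to 5.

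**Assumptions:** 1:1:1 allocation, so 30 per arm; mean group size m = 4; ICC of change 0.02, 0.05 or 0.10. The article states none of these.

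**1. The article's own figure, under independence.** The standardised difference has standard error √(2/30) = 0.258, so the noncentrality is 0.65/0.258 = 2.52. Power is about 71% by the normal approximation and 70% by the t distribution with 58 degrees of freedom (df). The stated 80% is not reproduced; it needs 38 to 39 per arm. The figure read as written therefore holds no spare allowance for clustering. This shortfall is a separate matter.

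**2. Design effect.** DE = 1 + (m − 1) × ICC = 1 + 3 × ICC.

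**3. True type I error if therapy group is ignored.**
- RL versus PSG (both arms grouped): 2[1 − Φ(1.96/√DE)].
- Active arm versus waitlist at T2 (one arm grouped): 2[1 − Φ(1.96/√((1 + DE)/2))].

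**4. Power for RL versus PSG.** Effective n per arm is 30/DE. The t distribution is used first with 58 df, then with df counted from therapy groups: 30/4 = 7.5 groups per arm, so 2 × 7.5 − 2 = 13.

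| Assumed ICC | 0.02 | 0.05 | 0.10 |
|---|---|---|---|
| DE | 1.06 | 1.15 | 1.30 |
| Type I error, RL v PSG | 5.7% | 6.8% | 8.6% |
| Type I error, active v waitlist, T2 | 5.3% | 5.9% | 6.8% |
| Effective n per arm | 28.3 | 26.1 | 23.1 |
| Power, 58 df | 67% | 64% | 58% |
| Power, 13 df | 62% | 58% | 53% |

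At ICC 0.01 the type I error for RL versus PSG is 5.3%. Over group sizes 3 to 5 and ICC 0.05 to 0.10 it runs from 6.2% to 9.8%.

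**5. Does the loss depend on the 70% baseline?** No. If 80% is taken as correct under independence, the noncentrality is 1.96 + 0.84 = 2.80. Dividing by √DE gives 2.72, 2.61 and 2.46. Subtracting 1.96 gives power of about 78%, 74% and 69% (normal approximation).

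**6. Interval width once clustering is modelled, RL versus PSG.** The ratio to the independence interval is √DE × t(13 df)/t(58 df) = √DE × 2.160/2.002. This is 1.16 at ICC 0.05 and 1.23 at ICC 0.10.

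**The case against.** **The model half is inferred.** The article never names the level of the random intercept, and an analysis plan that is not shown could include a therapy-group term. This stands as a limit on certainty. But the article does name a random structure, and the reason it gives for it concerns repeated measures. The power statement is firmer: it defines its contrast and standardiser with no clustering term.

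**No ICC is given.** A reader might infer that the standard errors are simply too small. The article does not support that unconditionally: it takes a positive ICC, and at 0.01 to 0.02 the inflation for RL versus PSG is 0.3 to 0.7 of a percentage point.

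**Age band and block.** Members of a therapy group also share an age band and a recruitment block, and a reader might count these as sources of inflation. They are not. Randomisation is individual, every block contains all arms, and both active arms use the age split. Ignoring a factor balanced across arms does not inflate error. Only what is specific to a therapy group, such as its dynamics, can do so. The practice effects foreseen in the Discussion largely follow calendar time, which concurrent arms share.

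**Clustering is limited by design.** One facilitator and manualised sessions remove between-therapist variation. This stands, and argues for modest ICC values, but it leaves peer dynamics untouched.

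**Conclusion.** The point holds in conditional form. Delivery creates therapy groups in RL and PSG, and neither the model, read plainly, nor the power figure reflects them. For ICCs of 0.05 to 0.10, RL versus PSG would be tested at about 7% to 9% instead of 5%, and an active arm versus waitlist at T2 at about 6% to 7%. Power for RL versus PSG would be about 58% to 64%, or 53% to 58% with degrees of freedom counted from therapy groups.

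These results rest on an assumed ICC, a mean group size of 4, equal allocation, and group membership that stays constant over the six sessions, which the format implies but the article does not state. A reader might also attribute the whole gap between the stated 80% and these power values to clustering. About ten points of it arise under independence; clustering with 58 df adds roughly 3 to 11 points over the assumed range.

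For a phase II trial of feasibility and efficacy, this should be fixed. It does not undermine the trial.

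**What to change.** **Statistical analyses section.** State the level of the random intercept and add a therapy-group random effect on post-baseline outcomes in a partially nested model. At T2, treat each waitlist participant as a singleton. At T3, assign former waitlist participants to the RL or PSG group they later joined, because by then they are grouped too. Fit by restricted maximum likelihood with Kenward-Roger or Satterthwaite degrees of freedom, since only about 15 groups inform RL versus PSG. Make the multiple imputation respect the same grouping.

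**Participants section.** Restate the power for 90 participants over an assumed ICC range. No extra enrolment is needed for this; the trial would report honestly what 90 can detect.

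**Cost.** Changes of wording, and a record of who attended which group. RL versus PSG intervals widen by about 16% at ICC 0.05 and 23% at ICC 0.10, partly because of the smaller degrees of freedom, and the published power becomes less favourable. If a group term is already planned, one sentence saying so settles the analysis half of the point.

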### Randomization

Participants will be randomised to one of the three study arms: a) Recapture Life-AYA, b) the PSG, or c) a waitlist condition. A flexible biased urn method of randomization, will be used, which adapts to the degree of imbalance between groups in a dynamic manner over the trial 
[50]. This method is superior to standard stratification in balancing groups across multiple covariates 
[51,52] whilst also being a suitable method when groups remain small 
[50,53,54]. This minimization will be based on four factors: (i) gender (male/female), (ii) severity of distress as measured by the Depression, Anxiety, Stress Scale-Short Form (DASS-21) intake interview (see below), (iii) time since treatment, classified into two groups, and (iv) degree of rural/remoteness as assessed by the Accessibility/Remoteness Index of Australia 
[55]. Participants will be randomised using electronic randomization used by independent personnel at the University of New South Wales.

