One challenge inherent in the design of this study will be to quantify the effect of support person (e.g., parent/caregiver) participation on AYA psychological outcomes. Parents/caregivers may have an important role in assisting AYAs to negotiate the disruption cancer causes in their normal trajectory toward independence 
[91]. Parent inclusion in skills-based programs also appears to increase their likelihood of improving AYA psychological outcomes 
[29]. However, in this trial the decision was made to make parent/support person participation optional, to facilitate and support the autonomy and independence of the AYA participants. This design may result in greater statistical complexity when attempting to delineate the impact of parental/support person involvement in AYA interventions.

Despite its strengths, the study design also has methodological vulnerabilities. The three-armed design of this trial, while a strength on the one hand, is also likely to increase the time it takes to recruit sufficient participant numbers. In addition, our decision to divide AYA participants into two defined age groups (15–18 and 19–25 years) may increase the time between recruitment and actual group participation.

The long-term, 12-month follow-up is another aspect of the study design that, although methodologically important, may add complexities to final data analyses. Participants may differ markedly in terms of the psychosocial support services they receive in this time, and the number of other AYA cancer survivors they come into contact with. Individual differences in terms of additional support services and peer support is a factor that is likely to be important throughout the trial as a whole. All of these factors will require careful monitoring and documentation, and will need to be taken into account in data analyses and interpretation.

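### As worded, the primary model contrasts change from T1 with only a random intercept: less precise than conditioning on T1 QoL, and T2 and T3 tests are mis-sized if visit correlations decay.

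*Protocol article*

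**What the plan says.** Three statements in the protocol article bear on this.

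- **Model and contrast.** Statistical analyses names mixed random-intercept models that will "assess differences between the groups in terms of change in QoL from T1 to T2, and from T1 to T3". It names no other covariance structure and does not say how T1 QoL enters, other than as the start of the change. T1 data are otherwise mentioned only for a separate exercise: "Multiple regression analyses will also be conducted using T1 data to identify demographic and other factors that contribute to treatment outcome".
- **Powered quantity.** Participants defines the effect, d = 0.65, as "the difference in change from T1 to T2 for any pair of groups, standardised on the pooled within-group standard deviation", to be detected "with a power of 80% at a significance level of 0.05 (two-tailed". The total is 90.
- **Allocation.** Randomization describes a biased-urn scheme: "This minimization will be based on four factors: (i) gender (male/female), (ii) severity of distress". Time since treatment and remoteness are the other two factors.

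Under Methods/Design, T2 falls seven weeks after T1 and T3 falls 12 months after participation in an active group.

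**The concern.** Two stated choices cost something.

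1. **Change from T1.** A group difference in change carries all the T1 noise. Under randomisation the arms share a T1 mean in expectation, so a model that uses this fact is never less precise in large samples, and is more precise whenever r is below 1. In a three-arm trial of 90, that precision matters.
2. **Random intercept only.** This covariance model has one variance and one correlation for every pair of visits. T1 and T2 are seven weeks apart, while T1 and T3 are more than a year apart. If the nearer pair is more strongly correlated, the pooled residual variance is too large for the T2 contrast and too small for the T3 contrast. The T2 contrast, on which the trial is powered, would then lose power, and the T3 contrast would reject too often.

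**Working it through.** **Inputs.** From the article: total 90, three arms, d = 0.65, two-sided 0.05, power 80%. Assumed: equal arms (30 each), equal visit variances, complete data, and all correlations, because the article gives none.

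**The plan's own figure.** With d on the SD of change, n per arm = 2(1.96 + 0.8416)²/0.65² = 37.2, so 38 per arm and 114 in total. At 30 per arm the power is 71% by the normal approximation and 70% by the noncentral t. The stated 90 is therefore not reproduced on this reading. It is reproduced if d is on the raw-score SD and r is about 0.6: the SD of change is then √(2 × 0.4) = 0.894, and 30 per arm gives 80.4%.

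**Precision.** Write σ² for the variance at each visit.

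- Variance of change: 2σ²(1−r).
- Variance of T2 given T1: σ²(1−r²).
- Ratio: (1−r²)/[2(1−r)] = (1+r)/2.

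For the same true difference, the effect in units of the smaller SD is 0.65 × √(2/(1+r)).

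| Assumed r | Variance ratio | Effective d | Power at 30 per arm (t) | n per arm for 80% (normal) |
|---|---|---|---|---|
| change score | 1 | 0.65 | 70% | 38 |
| 0.5 | 0.75 | 0.751 | 82% | 28 |
| 0.6 | 0.80 | 0.727 | 79% | 30 |
| 0.7 | 0.85 | 0.705 | 77% | 32 |

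If d is on the raw-score SD instead, the gain remains (normal approximation): 71% to 83% at r = 0.5, 80% to 88% at 0.6, and 90% to 94% at 0.7.

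**Test size under a random intercept.** With complete, balanced data the model in effect uses the mean of the three correlations, r̄. The true variance of a contrast divided by the variance the model assigns it is (1−r₁ₖ)/(1−r̄). The size is then about 2[1−Φ(1.96/√ratio)].

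- Correlations (T1–T2, T1–T3, T2–T3) of (0.7, 0.5, 0.5): r̄ = 0.567. For T2, 0.30/0.433 = 0.69, giving 1.9%. For T3, 0.50/0.433 = 1.15, giving 6.8%.
- Correlations of (0.7, 0.4, 0.5): r̄ = 0.533. For T2, 0.30/0.467 = 0.64, giving 1.5%. For T3, 0.60/0.467 = 1.29, giving 8.4%.

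A simulation (20,000 trials per row; three arms of 30, three visits) agrees:

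| Assumed correlations | T2 size | T3 size | T2 power, d = 0.65 on SD of change |
|---|---|---|---|
| 0.6, 0.6, 0.6 | 5.3% | 5.2% | 70% |
| 0.6, 0.4, 0.4 | 2.4% | 6.4% | 59% |
| 0.7, 0.5, 0.6 | 2.4% | 7.9% | 60% |
| 0.7, 0.5, 0.5 | 1.8% | 6.8% | 56% |
| 0.7, 0.4, 0.5 | 1.5% | 8.5% | 52% |

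In every row, a test using each contrast's own change SD stays at about 5%. The fault therefore lies in the pooled covariance and not in the contrast.

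**The case against.** The strongest reply is that this is one paragraph of a condensed article. It excludes nothing, and a mixed model with a common T1 mean also estimates a difference in change. An unconstrained change contrast is unbiased under randomisation and matches the quantity that was powered. Much of this stands: the precision point is about efficiency, and it applies to the default reading of the text. It does not dispose of the point, because the article does commit to a random intercept and a change contrast, and that default reading leaves T1 means free.

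The size results are also only illustrative. With equal correlations the tests hold 5%. The simulation has no missing data, although 20% attrition and multiple imputation are planned. Nor does it reflect the waitlist design: under Procedures, waitlist participants are re-allocated to an active group in Week 7, so they have no untreated T3. This also stands, and is why the mis-sizing is put conditionally.

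A reader might infer two stronger claims, and the documents support neither.

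- **That leaving out the minimisation factors overstates the standard error.** The article is silent on covariates, and such lists are commonly left to the full protocol or SAP. With T1 as a response and complete data, main effects of person-level factors also cancel from a within-person change. They help only through factor-by-time terms or in a baseline-adjusted model.
- **That the treatment effect will be adjusted for post-randomisation service use and peer contact.** The Discussion says only that these "will need to be taken into account in data analyses and interpretation". Describing them by arm would satisfy that sentence. It does not put them in the treatment-effect model.

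**Conclusion.** The point holds as a recommendation for a better primary model, not as an error that invalidates the trial.

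- **Precision.** Conditioning on T1 cuts the variance by (1−r)/2, which is 15–25% for r between 0.5 and 0.7. Power at 30 per arm rises from about 70% to 77–82%. This assumes equal arms, equal visit variances and d on the SD of change. On the raw-score reading the starting power differs, but the variance saving is the same.
- **Test size.** Size is correct under equal correlations. Under the decaying correlations worked above, the T2 test runs at about 1.5–2.4% with power of 52–60%, and the T3 test at about 6.4–8.5%. The direction follows from the model whenever T1–T2 is the strongest and T1–T3 the weakest (or equal weakest) correlation. The size of the error depends on values the documents do not give.

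**What to change.** State the primary model as a repeated-measures model for QoL at T2 and T3 with:

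- T1 Impact of Cancer Scale score as a covariate, with its own coefficient at each visit; or T1 kept as a response with its mean constrained equal across arms;
- an unstructured covariance over visits in place of the random intercept;
- REML with a small-sample degrees-of-freedom correction, such as Kenward-Roger;
- gender, intake DASS-21 distress, time since treatment and remoteness as covariates, since they drive allocation and can add precision once the model is baseline-adjusted.

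It would also help to say whether d = 0.65 is on the SD of change or of the raw score, and what r was assumed.

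The cost is wording and a few degrees of freedom. The article already plans the questionnaire at T1 and needs the four factors for allocation, so no patients, visits or measures are added.
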